### Procedures

Participants apply for inclusion in the study at the project website [48,49].

#### Informed Consent

After online registration, participants receive the patient information and informed consent form by direct mail. They are requested to sign and return the informed consent in a prepaid envelope. Also, they receive a registration confirmation by email with login details for the participant’s Web portal on the project website. Participants are requested to complete assessment T0a as a check on eligibility. Also, the participant’s medical doctor is consulted to check 3 of the eligibility criteria: finished curative-intent treatment for cancer more than 3 months ago, no current signs of cancer activity, absence of current or former major psychiatric disease.

#### Randomization

If the eligibility-criteria are met, the researcher confirms the participant’s enrollment. Subsequently, the activity sensor is given to the participant and its setup is explained in a face-to-face meeting in the participant’s home or another mutually convenient location. The second baseline assessment starts (T0b), followed by randomization of the participant to 1 of the 3 conditions by a script embedded in the researchers’ Web portal and uses the random function of php (rand(1,3)) [50]. The researchers can neither influence nor predict the outcome of the randomization process. Subsequently, the researcher emails the participant about the outcome of randomization, requests the participant to complete the third baseline assessment (T0c), and assigns the participant to a therapist in case the participant has been randomized to an experimental condition. Participants who do not fill out T0c are considered as not being included. The allocation of a therapist is based on current availability of the therapists who are involved in the trial.

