## Methods

### Design

A randomized controlled trial is performed including 3 parallel conditions: 2 experimental conditions (AAF and eMBCT) and a minimal intervention control condition. The intervention period is 9 weeks for all 3 conditions. Both experimental conditions are made as similar as possible in terms of time-investment and contact intensity with the therapist. Outcomes are self-reported and are Web-assessed at baseline (T0), 2 weeks post-intervention (T1), and at 6 months (T2) and 12 months (T3) after baseline. Figure 3 shows a schematic summary of the trial design.

The baseline assessment consists of 3 time-points: (1) T0a, the assessment to check eligibility; (2) T0b, the main baseline assessment taken after the eligibility check and informed consent, but naive of condition; and (3) T0c, directly after randomization for assessing the participant’s credibility and expectancy about the condition. All participants are invited to fill out short questionnaires in weeks 1, 2, 3, 4, 6, and 9 (Mi) of the intervention period in order to study mediation of the interventions.

After T2, patients in the control condition are offered 1 of the 2 experimental interventions, again in a research setting. Please note that the first 4 participants of this trial were randomized to 1 of the experimental conditions for the second semester, but to minimize dropout, all other patients will be allocated based on their own preference. During this second intervention period, these participants will again be assessed in weeks 1, 2, 3, 4, 6, and 9 (Mi’), the second week after the intervention (T1’), and 6 months after the second allocation (T2’). Participants in the control condition that are preferentially allocated to eMBCT after T2 do not wear the accelerometer during the second semester.

The protocol allows delay within the intervention period of a maximum of 2 weeks in case of, for example, illness or holiday. For all participants, the duration of their participation is approximately 12 months. Additional qualitative feedback will be obtained through explorative interviews with a subset of participants in the experimental condition shortly after T1 or T1’.

This trial was approved by the Twente Medical Ethical Committee (Enschede, the Netherlands) under number P12-26 and has been registered at The Netherlands National Trial Register under number NTR3483 [42].

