	Self-efficacy on activities	Selected items from the self-efficacy scales of Bandura [71] and Rodgers [72,73]: 13 items on a 0-100 NRS; subscales: planning and coping.	b		x		
	Catastrophizing	Fatigue Catastrophizing Scale [74,75] 9 selected items on a 5-point Likert scale.	b		x		
	Fear of cancer recurrence	Two selected items on a 7-point Likert scale [76].	b		x		
	Causal attributions	One self-conceptualized open answer question that translates to: “What do you consider as the cause of your fatigue?”	b		x		

^a^Baseline assessment T0 consists of 3 time-points: T0a: before eligibility check, T0b: after inclusion, and T0c: after randomization. T0c’ is assessed after preferential allocation.

^b^Mi and Mi’ = assessments at week (i=) 1, 2, 3, 4, 6, 9 of the intervention

^c^All physical activity measurements are blind except for the experimental activity feedback condition at M3, M6, and M9. In the second semester, M3’, M6’, and M9’ do not include a physical activity measurement in the mindfulness condition.

**Table 3 table3:** Other assessments.

Demographics, medical history, and control factors	T0^a^	T1/T1’	T2/T2’	T3
Age, gender, education, family status, nationality, time since diagnosis, time since previous treatment, fatigue duration, psychological counseling in the past, comorbidity.	a			
Cancer type, cancer treatment, perceived life threat of cancer (7-point Likert scale), known heredity of cancer (yes/no/don’t know), former experience with attention focusing exercise (yes/no), religious beliefs, perceived social support (Multidimensional Scale of Perceived Social Support [77]: 12 items on a 7-point Likert scale).	b			
Medication use, substance use (caffeine, nicotine, alcohol, drugs), quality of life (1 item on a 0-10 NRS).	a	x	x	x
Pain intensity and limitations by pain (2 items on a 7-point Likert scale), body mass index.	b	x	x	x
Life events since previous assessment, professional help received for fatigue outside the scope of the study protocol.		x	x	x
Perceived effectiveness of the intervention (5 items of which 1 item 0-10 NRS and 2 yes/no questions), perceived social support in following the intervention (1-10 NRS).		x		
Social desirability: 6 selected items from the Balanced Inventory of Desirable Responding [78] on 5-point Likert scale.			x	

^a^Baseline assessment T0 consists of 3 time-points: T0a: before eligibility check; T0b: after inclusion; and T0c: after randomization.

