##### Descriptives

Quantitative analyses will be conducted on an intention-to-treat basis. A flow diagram following the CONSORT guidelines will be included. Descriptive statistics will be calculated and presented. Independent samples’ t-tests and χ^2^ tests will be performed to check for baseline differences between the respective experimental conditions and the control condition with respect to demographic variables (eg, family status, age, gender, and level of education), time since end of treatment, and baseline levels of the outcome variables. If we find statistically significant differences in the mean of fatigue severity across baseline descriptives, dummy variables will be added to the model as covariates to control for these differences.

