#### Core Analysis

##### Effectiveness

###### Overview

Five steps will be taken to evaluate the effectiveness of both interventions, which are explained here in a generic way. The specific hypotheses on the effectiveness of the interventions in our study are shown in Textbox 1.

Hypotheses on effectiveness.
*Primary outcome*
In both experimental conditions:Fatigue severitydecreases during the intervention, andremains decreased after 6 months.After 6 months, fatigue severity has decreased significantly more compared to the control condition.After 6 months, more participants show a clinically relevant reduction of fatigue severity compared to the control condition. A patient is considered clinically improved if he or she has a reliable change index of more than 1.96, according to the reliable change index, and the end score has to be within the normal range, that is a score < 1 standard deviation above the mean of a normative group [94] (ie, a score < 30.4 on the CIS fatigue severity subscale [51]).
*Secondary outcomes*
For both interventions we expect that:After 6 months, mental health and work ability have improved more than in the control condition.After 12 months, fatigue severity, work ability, and mental health remain improved in both intervention groups.Improvements in mental health and work ability after 6 and 12 months are related to reductions in fatigue severity.Return to work and reduced absenteeism will be studied as explorative outcomes.

###### Step 1

Overall effectiveness will be tested in an intention-to-treat analysis by a multiple group latent growth model [79] using data from the first semester. This technique allows individuals to have an individual growth trajectory over time and compensates for missing data in an elegant way.

Since different growth patterns are expected for the pre-intervention period, the intervention period, and the post-intervention period, we will apply piecewise growth modeling so that a slope factor will be estimated for each of the 3 periods (Figure 4). Initial intercepts will be configured to represent the T0b score. This intercept and the pre-intervention slope factor will be constrained to be equal between all 3 conditions (and this assumption will be checked), whereas the subsequent slope factors will be estimated separately for the 3 conditions.

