The fit of the piecewise model will be compared with a quadratic model. In the quadratic model, the entire first semester is modeled with 1 slope factor and 1 quadratic factor for each of the 3 conditions and an intercept that represents T0b and is constrained similarly to the piecewise model.

Both models will be run both with and without using time-varying loadings in order to check whether corrections should be made for differences in timings between the questionnaires. Growth factor estimates and model fits for all 4 models will be reported (Table 5).

Neither the participants nor the researchers ([name] and MW) are blinded to allocation. Therefore, an independent statistician ([name]) who is blind to the allocation will test the primary hypothesis.

The same procedure will be followed for the secondary outcomes, except that the initial intercept of mental health will represent T0a, rather than T0b, because T0b does not include an assessment of mental health.

Results of frequentist analyses will be reported by *P*-values (significant in case <.05) and with 95% confidence intervals. Parameter estimates of models by means of Bayesian estimators will be reported with 95% central credibility intervals.

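### Randomized participants who do not complete T0c are counted as not included, a post-randomization exclusion that contradicts the stated intention-to-treat analysis

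*Protocol article*

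**What the plan says.** The Randomization section of the protocol article gives the order of events: the T0b assessment, randomization by script, an email from the researcher disclosing the arm together with the request for T0c, and then the rule "Participants who do not fill out T0c are considered as not being included".

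The Design section describes the questionnaire as "T0c, directly after randomization for assessing the participant’s credibility and expectancy about the condition". Step 1 of the effectiveness analysis begins its blinding statement with "Neither the participants nor the researchers" and says that these parties know the allocation; only the statistician who tests the primary hypothesis is blinded.

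On the analysis set, Descriptives says "Quantitative analyses will be conducted on an intention-to-treat basis". Step 1 says "Overall effectiveness will be tested in an intention-to-treat analysis by a multiple group latent growth model". Step 3, on the proportion with clinically relevant improvement, again specifies intention-to-treat.

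On the meaning of inclusion, the footnote to Table 2 reads "T0b: after inclusion, and T0c: after randomization", which places inclusion before T0b and so before randomization. The Results section counts 111 people as included in January 2015 and says that 19 had not yet been randomized.

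**The concern.** Intention-to-treat means analysing everyone randomized in the arm to which they were assigned. The T0c rule makes membership of the trial depend on something that happens after randomization, after the arm is known, and that consists of giving an opinion about that arm. Whether a person completes it could therefore depend on the allocation. If it does, and if non-completers would have had different fatigue at 6 months, the groups compared are no longer those that randomization formed.

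The rule has no evident purpose for the primary analysis. Fatigue severity is measured at T0a and T0b, before allocation, and the growth model tolerates missing values. Credibility and expectancy are asked again in weeks 1, 2 and 4, so a missing T0c costs one early value of one mediator. A further risk is that people regarded as not included may fall outside the follow-up that the Nonadherence and Withdrawal section arranges for those who stop or withdraw.

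**Working it through.** **1. Does anything restore these participants?** The Randomization rule, the two general intention-to-treat statements and Step 3 were set side by side. Nothing in the article returns T0c non-completers to the analysis. The rule and the stated analysis set cannot both hold on a plain reading.

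**2. Is inclusion used consistently?** Group sizes in the Results: 36 + 24 + 32 = 92 randomized; 92 + 19 not yet randomized = 111, the number given as included. The 19 cannot have completed T0c, which follows randomization. Inclusion here, as in Table 2, precedes randomization, whereas the Randomization section withdraws it afterwards.

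**3. Does the sample-size reasoning allow for this loss?** The plan's retention figures reproduce:
- 330 / 3 = 110 per arm
- 110 × 0.70 = 77 per experimental arm and 110 × 0.85 = 93.5 (stated as 94) in control at T2
- 77 + (94 / 2) × 0.70 = 109.9 (stated as 110) completing each intervention
- 220 × 0.90 = 198 completing the trial

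No step covers loss at T0c, and no rate is given anywhere.

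**4. How large could the bias be?** Let s be the share not completing T0c in an arm, and d the mean 6-month outcome of non-completers minus that of completers. The completers' mean equals the full-arm mean minus s × d. The contrast between experimental (E) and control (C) arms therefore shifts by s_C × d_C − s_E × d_E, which is (s_C − s_E) × d when d is the same in both arms.

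Assumed inputs, not from the article: a gap in s of 5 to 20 percentage points and d of 3 to 8 CIS points.
- Low end: 0.05 × 3 = 0.15 points
- High end: 0.20 × 8 = 1.6 points

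With equal shares and equal d the shift is zero. With equal shares but different kinds of people lost in each arm it is s × (d_C − d_E), which need not be zero.

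**5. Illustration as type I error.** Assume no true effect, 110 randomized per arm, outcomes seen for all who complete T0c, no T0c loss in the experimental arm, and a comparison of two means by normal approximation. In SD units the standard error is √(1/n_E + 1/n_C), where n_E and n_C are the numbers remaining.

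| T0c loss, experimental vs control | d (SD) | Bias (SD) | Standard error (SD) | Two-sided type I error |
|---|---|---|---|---|
| 0% vs 5% | 0.5 | 0.025 | √(1/110 + 1/104.5) = 0.137 | 5.4% |
| 0% vs 10% | 0.5 | 0.05 | √(1/110 + 1/99) = 0.139 | 6.5% |
| 0% vs 20% | 1.0 | 0.20 | √(1/110 + 1/88) = 0.143 | 28.8% |

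The last row is an extreme case. These rows illustrate the mechanism and are not estimates for this trial.

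**6. Does keeping the baseline scores suffice?** Step 1 constrains the intercept and the pre-intervention slope to be equal across arms. People with only T0a and T0b scores inform mainly those factors. The model fills in their later course from people in the same arm with similar baselines. If non-completers differ in ways that baseline fatigue does not capture, most of the shift in step 4 remains. Only later outcomes remove it.

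**The case against.** The sentence stands under Procedures, not in the Analysis Plan, and does not literally say that these people are excluded from analysis. The Eligibility section does say so explicitly for pregnancy and recurrence. Since inclusion is used loosely elsewhere, one could read the rule as administrative. This weakens the claim that removal is explicit. It does not supply another plain meaning for a randomized person who is declared not included, and the loose usage is itself something to correct.

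A reader might go further and infer that skipping T0c is a reaction to the allocation, for instance disappointment with the email-only control, and that people are removed selectively by arm. The article does not support this. It gives neither a rate nor reasons, and illness, login trouble or forgetting are equally possible. Its only arm-specific expectation is 30% attrition in the experimental arms against 15% in control. That concerns loss during the intervention and, if anything, points the other way. Controls are also offered an intervention after T2.

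A reader might also infer that the flow diagram will hide these losses. Descriptives promises a CONSORT diagram, and nothing says that T0c non-completers will be left out of it.

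Finally, the size rests wholly on assumed inputs. Setting it against the 4.6 points between the entry score and the normal-range cut-off (35 − 30.4) would not help, because that distance is neither a treatment effect nor a measure of precision. All of these limits stand. None removes the contradiction between the rule and the stated analysis.

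**Conclusion.** The concern holds as a contradiction in the plan. On its plain reading the T0c rule excludes randomized participants on the basis of a response given after they know their arm, while the general analysis statement, the primary growth model and the responder analysis are all declared intention-to-treat. The rule also conflicts with the article's own use of inclusion in Table 2 and the Results.

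The resulting bias is possible but not demonstrated. It is zero if non-completion is unrelated to both arm and prognosis. Under the assumptions in step 4 it is about 0.15 to 1.6 points on the 8 to 56 scale. As the plan stands, a reader cannot tell where in that span, or below it, the trial lies. Because the rule determines who enters the primary comparison, it should be corrected before the analysis, whatever its eventual size.

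**What to change.** - Delete the sentence from the Randomization section, and use inclusion throughout for the step before randomization.
- Define the analysis set for Steps 1 to 3 as everyone randomized, in the arm assigned. The separate exclusion for pregnancy or recurrence under Eligibility is not settled by this point, but the definition must state how the two relate.
- Treat a missing T0c only as a missing credibility and expectancy value.
- Apply the Nonadherence and Withdrawal procedure to T0c non-completers: ask for T1, T2 and T3, or at least the CIS fatigue severity subscale. Without this the randomized set is restored in name, but most of any bias remains.
- State how Step 3 counts people with no 6-month score.
- Report T0c non-completion by arm in the CONSORT diagram, and show the as-included set as a sensitivity analysis.

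The cost is a change of text, a little more follow-up work and more missing outcome data in the primary model. Recruitment began in 2013, so outcomes of participants already dropped without follow-up may not be recoverable. Their number by arm should be reported, with the loss stated as a limitation.

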#### Research Conditions

Both experimental conditions are described in the Introduction and will be described more extensively in an article on eMBCT by [name] et al [34], and a paper on the development of the AAF intervention by [name] and [name] (in press) [36].

#### Active Control Condition

Patients who are assigned to the control condition receive weekly emails containing standard psycho-educational texts about CCRF in order to minimize the dropout rate, following the design of Postel et al [51]. An example of the information that is offered in this minimal intervention control condition is given in Multimedia Appendix 4 and overlaps completely with the information that is given during both experimental interventions. This condition controls for receiving information on CCRF and for being involved in eHealth research.

#### Nonadherence and Withdrawal

Participants who do not adhere to, or withdraw from, the study or the intervention are contacted by phone and asked for the reason for nonadherence or withdrawal. Participants who want to stop with the intervention are asked to complete a post-intervention assessment at T1 and follow-up assessments at T2 and T3. Participants who withdraw from the study are asked to answer the questions of the fatigue severity subscale of the CIS online or during a telephone conversation.

### Assessments

All self-reported questionnaires are Web-assessed via a Web portal on the project website [48,49], developed by Roessingh Research and Development. Participants receive an email when an assessment becomes available and can log in to the Web portal to complete the questionnaires. During the intervention period, each assessment is available for 1 week, but can stay open longer if therapy is postponed due to, for example, illness or holiday. If a participant has not completed it within 6 days, he or she is reminded by email at least once to complete the questionnaire. Within each assessment, the questionnaires are grouped on the basis of importance and subject. Item sequences of the questionnaires for the mediating factors and outcome measures differ between the assessments. Personal data is stored separately from the research data. An overview of all the assessments is shown in Tables 2 and 3.

Physical activity data is collected using the same device as that used for the ambulant activity feedback therapy: a 3D-accelerometer (ProMove 3D) combined with a mobile phone that collects the accelerometer data and sends it to a secured Web server at Roessingh Research and Development [52]. However, the mobile phone does not give feedback on activity, but does state whether the system is working properly and sends an error message if the connection to the sensor fails. Participants are reminded by email to wear the accelerometer on the day before the start of the week in which they will be using it.

### Outcome Measures

#### Fatigue

Fatigue severity will be assessed with the CIS, which consists of 20 items that score on a 7-point Likert scale [53,54]. The CIS has 4 subscales (fatigue severity, motivation, concentration, and physical fatigue) of which the fatigue severity subscale will be used as the primary outcome (8 items, range: 8-56 points). The CIS has shown good discriminative validity in a working population [55], is sensitive to changes in the chronic fatigue syndrome population [56], and has previously been used with cancer survivors [7,57]. The CIS strongly resembles the Multidimensional Fatigue Inventory, which is often used in international studies [54]. Fatigue severity will be assessed at T0a, T0b, M3, M6, M9, T1, T2, and T3. However, the other 3 subscales will only be assessed at T0b, T1, T2, and T3.

